## Abstract

**Background:** Breast cancer is the most common cancer type among women with >1million new cases worldwide. More than 40% of them will struggle with pain and fatigue years after surgery, regardless of surgical procedure. These consequences are detrimental and result in distress and disability, including work disability. Few previous attempts have been made to prevent persistent pain and fatigue after surgery by applying a psychological approach, despite psychological risk factors being crucial in the development of both persistent pain and fatigue. In this study, we aim to develop and test an easily implementable strategy of preventing persistent pain and fatigue after breast cancer surgery. The intervention strategy involves a pre-operative hypnosis session and a web-based post-operative Acceptance and Commitment Therapy. The hypnosis was previously found effective in alleviating acute post-operative pain and fatigue in breast cancer patients, while ACT may be particularly well suited to cancer populations as it offers a model of healthy adaptation to difficult circumstances. Together they form an intervention strategy with both a preventive and a rehabilitative focus.

**Methods/design:** The study will be run as a randomized controlled trial where effects of the pre- and post- operative interventions will be compared to attentional control and treatment as usual (TAU). Patients will be randomized to receive either a brief hypnosis session before surgery, and a web-based psychological intervention after surgery (ACT), or mindfulness meditation administered through a mobile app before surgery and TAU after surgery. Measurement, in the form of self-reported data and biomarker data will be assessed pre-surgery, post-surgery and 3 and 6 months after surgery.

**Discussion:** This study will be the first study to combine a pre-operative hypnosis with a post-operative ACT to prevent pain and fatigue after breast cancer surgery. The results from our study might i) help the large group of women affected by chronic pain and fatigue after breast

cancer surgery, ii) shed light on the mechanisms involved in chronic pain development, and  
iii) serve as a model for other surgical procedures.

**Trial registration:** The project will be registered in a relevant international trial register.

**Keywords:** Breast cancer; pain; post-surgical pain; fatigue; hypnosis; acceptance and  
commitment therapy

## Background

Breast cancer is the most common cancer type among women, with >1 million new cases worldwide every year (1). Survival rates for breast cancer is increasing (2), but for many patients survivorship is also characterized by disabling psychological and physical late effects (3-5). Chronic post-surgical pain (CPSP) and persistent fatigue have the most profound prevalence. CPSP has prevalence rates ranging from 25-60% depending on definition, measurement and treatment (6). In a recent Norwegian study, more than 40% of women treated for breast cancer continued to have pain 2-6 years after surgery (7), while over a third of the women in a large Danish study reported persistent pain 5-7 years after surgery (8).

Persistent fatigue is the most common symptom associated with cancer and its treatments (9). Still, studies on the occurrence of and predictors of fatigue after surgery are scarce. One of the few studies investigating persistent fatigue after surgery reported high levels of fatigue in the first two months after surgery, followed by mild-to-moderate levels of fatigue that persisted 12 months after surgery (10). In another post-operative study, a third of the women struggled with persistent fatigue up to 10 years into survivorship (11)

The pathophysiology of CPSP is still unclear. Presumably, the nature of most CPSP is neuropathic since surgery (e.g. mastectomy) may involve major nerve damage, and is associated with the highest incidence of such pain (12, 13). However, many patients with CPSP do not show any signs of neuropathic pain, or any sensory changes (3). It is thus assumed that the distinct pathophysiology reflects both peripheral and central sensitization as well as humoral factors contributing to pain. Further, the etiology of chronic pain is grounded in the bio-psycho-social model, where psychological and social factors contribute to the

development of CPSP (14). The pathophysiology of post-surgical fatigue is also largely unclear (15). The underlying mechanisms likely vary from patient to patient, with a mixture of biological and psychological underpinnings (16). Interestingly, there are several shared risk factors between pain and fatigue after surgery, including depression and outcome expectancies (17), implying that the very same processes might influence both post-surgical pain and fatigue.

Unmodifiable risk factors for CPSP involve female gender and younger age (12), as well as preoperative pain conditions and use of opioids (12, 13, 18, 19). However, a preventive intervention could target psychological factors, which are both modifiable, robust and potent predictors of CPSP and fatigue (14, 20). The most frequent tap into anxiety, such as hypervigilance and pain catastrophizing (20-24). Other strong predictors involve depression, stress, and optimism (10, 14, 23).

Despite strong evidence supporting the role of psychological factors in the development of CPSP and fatigue, hardly any studies have investigated psychological and behavioral interventions aimed at preventing these symptoms. CPSP and fatigue *management*, however, has been the aim of several psychological and behavioral interventions. Mindfulness-based cognitive therapy on persistent pain after breast cancer surgery was recently found effective in reducing pain intensity (25), and a study led by a member of our project group found beneficial effects of CBT plus hypnosis to control fatigue in patients undergoing radiotherapy for breast cancer (26). Several studies of similar psychological interventions exist, but with limited effects (27, 28), and with no preventive focus (29-31).

Hypnosis is a non-pharmacotherapeutic technique that holds promise as a harmless and effective pre-operative intervention to alleviate acute post-surgical pain and fatigue (32, 33). Clinical research with at least 20 different surgical populations has indicated that hypnosis can reduce the need for medication, reduce post-surgical symptoms, and enhance recovery (33). Furthermore, meta-analyses (34), narrative reviews (35, 36), and randomized clinical studies (37-40) all support the potential clinical utility of hypnosis with surgical breast cancer patients. A rigorous trial from 2007 demonstrated particularly large effects of a specific 15-minute pre-operative hypnosis on analgesic needs, pain intensity and fatigue after breast cancer surgery (41). However, the results from this trial have not been replicated, and results from hypnosis trials in general lack long-term follow-up.

Acceptance and Commitment Therapy (ACT) is an evidence-based treatment for persistent pain (42, 43) and is also a good fit for treating persistent fatigue (44). ACT is well suited to cancer populations as it offers a model of healthy adaptation to difficult circumstances and has shown promise in the treatment of opioid misuse (45). There have been several calls to expand the scope of ACT interventions to the treatment of CPSP (46). In a recent initiative, ACT was applied as treatment for CPSP in The Toronto General Hospital, with preliminary promising results. Those receiving ACT demonstrated greater reductions in opioid use and pain interference, as well as reductions in depressed mood, compared to those who received treatment as usual (follow-up from medical doctor) (47, 48). In addition to being an evidence-based treatment for pain and fatigue, ACT is also among the very few psychological treatments with documented effects on return-to-work (49). Moreover, in a Norwegian study from members of the project group, a miniscule ACT follow-up intervention consisting of 1-6 phone calls, eased patients transition into the workplace (50)

Despite the fact that both CPSP and persistent fatigue are common consequences of breast cancer surgery (7, 15), with disabling effects on recovery outcomes and quality of life, hardly any studies have looked at preventive interventions from a psychological perspective. As psychological risk factors are vital, and the pathophysiology of both conditions largely unknown, interventions focusing on the psychological factors are largely needed.

## **Methods/Design**

### **Aims and objectives**

The primary aim of the study is to develop and test an easily implementable strategy of preventing persistent pain and fatigue after breast cancer surgery. The intervention strategy involves a pre-operative hypnosis session and a post-operative, internet-based Acceptance and Commitment Therapy (iACT). The hypnosis was previously found effective in alleviating acute post-operative pain and fatigue in breast cancer patients, while ACT may be particularly well suited to cancer populations as it offers a model of healthy adaptation to difficult circumstances. Together they form an intervention strategy with both a preventive and a rehabilitative focus.

We have the following hypotheses:

- 1) Hypnosis is more effective than one-session mindfulness in relieving acute post-surgical pain and fatigue
- 2) Hypnosis alters markers of bodily stress responses and impacts immune reactivity associated with pain and fatigue.
- 3) Hypnosis + iACT results in less post-surgical pain and fatigue and fewer medical prescriptions for pain medication 3 months after surgery compared to one-session mindfulness + TAU

- 4) Hypnosis + iACT is favorable in a cost-utility analysis, and will result in fewer days of sick leave at 1 year follow-up compared to one-session mindfulness + TAU
- 5) Hypnosis + iACT results in less psychological distress and fewer medical prescriptions for psychotropic medications at the 3 and 6-month follow-ups compared to one-session mindfulness + TAU

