## **Design**

The study design involves a sequential, multiple assignment, randomized trial (SMART), where participants are randomly assigned to a treatment option at two stages, both pre- and post-surgery. By randomizing participants multiple times, we can assess the effectiveness of both interventions at each stage. We will thus be able to assess the short and long-term effectiveness of the pre-operative hypnosis, both alone and in combination with the post-operative iACT. Similarly, we will be able to assess the effectiveness of the post-operative iACT, both alone and in combination with the pre-operative hypnosis.

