## **Randomization**

The randomization procedure will be administered through the program Viedoc that uses an automated and valid randomization procedure. We intend to use a stratified randomization method in order to balance the influence of covariates. The main covariates of interest here is type of surgery (mastectomy vs breast-conserving surgery) and whether the newly diagnosed breast cancer is a relapse or not. Stratified randomization is achieved by generating a separate block for each combination of covariates, and subjects are assigned to the appropriate block of covariates. After all subjects have been identified and assigned into blocks, simple randomization is performed within each block to assign subjects to one of the groups. Furthermore, a SMART randomization procedure will be applied, where the participants are randomized twice – pre-operative (hypnosis vs a one-session mindfulness), and post-operative (iACT vs treatment as usual).

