#### *Post-surgical intervention*

After surgery, participants will be randomized again to either a post-surgical intervention or to treatment as usual. The post-surgical intervention is comprised of a web-based ACT intervention with the cognitive activation model of stress as theoretical vantage points. The intervention consists of videos in combination with a work booklet targeting three main processes derived from the ACT hexaflex model (57), and delivered in two stages. In the initial stage, the intervention has several videos that is built to involve the patient in a broadening of their perspective of what can constitute maintaining and debilitating factors when experiencing persistent pain and/or fatigue. These initial videos involve a biopsychosocial explanation of pain and fatigue, alongside an introduction to mindfulness, values-based living, and stress reduction through cognitive behavioral techniques.

The next stage of the intervention involves the use of a hand-out booklet that serves as an addition to numerous videos presented to the participants. The videos are sorted in three categories aimed to communicate the six processes in a commonsensical, patient friendly way. The three categories are referred to as the tri-flex in the Focused ACT model (58), and consists of Aware (present-moment awareness and self-as-context), Open (Accept and defusion) and Engaged (values and committed action).

Within the booklet there are written tasks corresponding to different videos and scenarios shown in the online intervention to approximate previous trials showing efficacy on chronic pain from a similar intervention (59).

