### ***Health Economic analysis***

The health economic analyses will investigate differences in treatment costs, as well as indirect costs related to work (dis)ability and sick-leave. The cost-utility analysis will be performed according to well-established methods, taking into account the direct (pre- and post-operative interventions) costs and quality of life (generated from EQ-5D). performed estimating costs per quality-adjusted life year (QALY).

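### Hypothesis 4 names only mindfulness + TAU as comparator although four strategies are randomised, so the planned cost-utility analysis need not show whether the second component is worth adding to the first

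*Protocol*

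**What the plan says.** Hypothesis 4 (Protocol, Aims and objectives) claims that "Hypnosis + iACT is favorable in a cost-utility analysis, and will result in fewer days of sick leave at 1 year follow-up". The sentence closes with its only comparator: "fewer days of sick leave at 1 year follow-up compared to one-session mindfulness + TAU".

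The design is wider than that comparison. Under Design, "participants are randomly assigned to a treatment option at two stages, both pre- and post-surgery". Under Randomization, women are "randomized twice – pre-operative (hypnosis vs a one-session mindfulness), and post-operative (iACT vs treatment as usual"). The Post-surgical intervention section confirms it: "After surgery, participants will be randomized again to either a post-surgical intervention or to treatment as usual". The stated reason for the two stages is that "we can assess the effectiveness of both interventions at each stage", with each component studied alone and combined with the other. That passage speaks of effectiveness and does not mention costs.

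The Health Economic analysis section plans a cost per QALY, "taking into account the direct (pre- and post-operative interventions) costs and quality of life", with quality of life from EQ-5D. Neither it nor Statistical analyses names a comparator or describes an incremental comparison across strategies.

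The Abstract describes two arms only (package, or mindfulness app followed by TAU), and Sample size and power plans two groups of 100.

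**The concern.** A cost-utility analysis serves a choice among the options that can be adopted. If everyone is randomised at both stages, a hospital could adopt hypnosis with usual follow-up, iACT without hypnosis, both, or neither, and the trial will hold data on all four. Comparing both with neither answers a legitimate question, but it merges two decisions. One efficient component can carry the other, and the merged ratio will not reveal it. At stake is a conclusion that the package is favourable when the trial's own data could show that one component alone gives the same QALYs for less.

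**Working it through.** **1. Number of strategies.** Two options before surgery times two after gives 2 × 2 = 4: hypnosis + iACT, hypnosis + TAU, mindfulness + iACT, mindfulness + TAU. Hypothesis 4 refers to the first and the last. No section compares cost per QALY for the package with either of the middle two.

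**2. Why the single comparison is not enough.** Let NB be net benefit at threshold λ (λ × QALYs − cost). For either component taken first, this identity holds whether or not the effects add up:

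NB(package vs neither) = NB(first component vs neither) + NB(second component added to the first)

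The left side can be positive while the last term is negative. The stated comparison estimates only the left side.

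**3. Illustration.** The protocol gives no costs, QALYs or threshold, so every value here is assumed, in arbitrary cost units. The order of components is also arbitrary: the documents do not say which costs more.

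- First component vs neither: cost 100, gain 0.010 QALY.
- Second component added to the first: cost 300, gain q.
- Threshold: 50,000 per QALY.

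| q (assumed) | Package vs neither | Second added to first |
|---|---|---|
| 0 | 400/0.010 = 40,000 | +300 for no gain: package dominated |
| 0.003 | 400/0.013 = 30,769 | 300/0.003 = 100,000 |
| 0.006 | 400/0.016 = 25,000 | 300/0.006 = 50,000 (break-even) |
| 0.010 | 400/0.020 = 20,000 | 300/0.010 = 30,000 |

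The package passes against neither when 50,000 × (0.010 + q) ≥ 400, that is q ≥ −0.002. The second component is worth adding when 50,000 × q ≥ 300, that is q ≥ 0.006. Between these values the two comparisons give opposite answers. At q = 0 the package's net benefit is 50,000 × 0.010 − 400 = 100, against 50,000 × 0.010 − 100 = 400 for the first component alone. With other inputs the interval moves, and it may be wide or negligible.

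**4. Precision.** The protocol gives no sample-size figure for the cost-utility analysis. Its pain figure reproduces: a 1-point difference, SD 2.4, two-sided 0.05 and 80% power need 91 per group by the normal approximation and 91.4, rounded up to 92, by the t-test; 92 is stated. That figure is for two groups.

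Assuming 1:1 at each stage (no ratio is stated), 200/4 = 50 women per strategy before attrition. In units of the SD of net benefit:

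- Any two-strategy contrast: SE = √(1/50 + 1/50) = 0.20.
- One component's effect in an additive model on all 200: SE = √(1/100 + 1/100) = 0.14.
- Package vs double control in that additive model, as the sum of two orthogonal effects: SE = √(0.02 + 0.02) = 0.20, the same as the two-strategy contrast.

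For scale, a two-strategy contrast on pain with the protocol's own inputs has about 55% power at 50 per strategy, against 84% at 100 per group.

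**The case against.** **The comparator may not be fixed at all.** Grammatically, the comparator in hypothesis 4 can attach to sick leave only. A reader might infer that the protocol restricts the cost-utility analysis to package versus double control; the text does not establish that, and the analysis sections exclude nothing. Hypotheses 3 and 5 use the same comparator, which makes the joint reading plausible. On the narrower reading the cost-utility comparator is unstated, the component comparison is still absent, and the same amendment helps.

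**This detail belongs in a SAP or health economic plan.** Ordering of ICERs and handling of dominance often do, and their absence alone would be no finding. The comparator, however, appears in a protocol hypothesis, and a later plan that followed it on the joint reading would carry the limitation forward.

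**The component contrasts under Design would expose a useless component.** Partly true. They cover effectiveness, though, and a component can have some effect and still not be worth its cost.

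**The package is the strategy of interest.** This stands: the aim is framed around the combined strategy, so its comparison with the double control should be kept.

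**Stronger readings that do not hold.** A reader might infer that using about 100 of the 200 women costs precision. It does not for this contrast: the SE is 0.20 SD either way. A reader might also infer that the trial will recommend an inefficient package, or that iACT is the part that adds cost without benefit. The protocol states no recommendation rule and gives no cost or QALY for either component.

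**Conclusion.** The point holds as a gap that is cheap to close. On the protocol's text, the package's cost-utility need only be set against mindfulness + TAU, or against a comparator left unstated. Neither reading provides the comparison that shows whether both components are needed. A package dominated by one of its components could therefore be called favourable. This is a possibility: it arises when one component adds cost with little or no QALY gain. Its likelihood and size cannot be derived from the documents.

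The conclusion assumes that the two-stage randomisation is what will be run. If the Abstract's two arms were correct, the two single-component strategies would not exist in the data and the incremental analysis would be impossible. That contradiction must be settled first. The cost-utility question is not one of the primary outcomes, so this should be amended but does not threaten the main analysis.

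**What to change.** 1. Reconcile the Abstract, and the two groups in Sample size and power, with the two-stage design.
2. In hypothesis 4, state which comparator applies to cost-utility and which to sick leave. Keep package versus mindfulness + TAU.
3. In hypothesis 4 and Health Economic analysis, add a full incremental cost-utility analysis of the four randomised strategies: rank by cost, remove dominated and extendedly dominated options, and report each ICER against the next non-dominated option.
4. Estimate it from a net-benefit model with both allocations and their interaction, at stated thresholds. Use the additive model as a sensitivity analysis only: as the main model it would force the package's value to equal the sum of its parts, which is part of what is being asked.
5. Show the uncertainty, and base any cost-utility conclusion about the package on the incremental comparison.

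Cost: protocol wording and some extra analysis, with no new patients and no data beyond the costs and EQ-5D on which the Health Economic analysis section already relies. EQ-5D is not described under Outcome Measures, so its collection is assumed here. The downside is imprecision with about 50 women per strategy (1:1 assumed), and the package may turn out not to be the preferred strategy.

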## **Design**

The study design involves a sequential, multiple assignment, randomized trial (SMART), where participants are randomly assigned to a treatment option at two stages, both pre- and post-surgery. By randomizing participants multiple times, we can assess the effectiveness of both interventions at each stage. We will thus be able to assess the short and long-term effectiveness of the pre-operative hypnosis, both alone and in combination with the post-operative iACT. Similarly, we will be able to assess the effectiveness of the post-operative iACT, both alone and in combination with the pre-operative hypnosis.

## **Outcome Measures**

To assess hypothesis 1, subjective experiences of pain intensity, pain unpleasantness, and fatigue will be assessed using the Numerical Rating Scale (NRS) and Visual Analogue Scales (VAS) after surgery, upon discharge. Both intensity (i.e., amount) and unpleasantness of pain will be assessed to capture its sensory and affective dimensions. Two 100-mm visual analog scales (VASs) will be used to assess fatigue and muscle weakness, in line with previous breast cancer trials of post-surgical fatigue (26, 41).

To assess hypothesis 2, we will measure cortisol in hair as a marker of hypothalamus-pituitary-adrenal (HPA) axis activity, and two measures of inflammation – high sensitive CRP

(hs-CRP) and lipopolysaccharide (LPS) reactivity. We consider hs-CRP an acceptable initial marker of systemic inflammation, whilst LPS will provide more nuanced and detailed results of immunological reactivity.

To assess hypothesis 3, NRS will be used to measure post-surgical pain, and FACIT-F (51) to measure post-surgical fatigue at 3 months follow-up. Registry data on pain-related prescriptions will further be extracted from The Norwegian Prescription Database (NorPD).

To assess hypothesis 4, we will use registry data to estimate the number of days participants in each group have been on sick leave (or other welfare benefits) during the year following surgery.

To assess hypothesis 5, we will measure psychological distress by the Hospital Anxiety and Depression Scale (52), as well as data on psychotropic prescriptions from The Norwegian Prescription Database (NorPD).

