### **Data collection and management**

Self-reported data and biomarker data will be collected pre-surgery (questionnaires, hair and blood), post-surgery upon discharge (brief phone survey), 3-4 weeks after surgery (blood), as well as 3 and 6 months after surgery (only questionnaire data). These time points either align with clinical follow-ups at the outpatient oncology department, or are responded to through an

electronic link in the patients' homes to avoid unnecessary strain on the patient. Patient charts will be used to collect data on surgical procedures and potential complications during/after surgery. This will include information about the duration of the surgery, tumor-related variables, severity of acute post-surgical pain, and other relevant intra-operative variables. Registry data on employment and benefit take-up and medical prescriptions will be obtained from FD-Trygd and the Norwegian Prescription Database (NorPD), respectively. To be able to assess for the effects of the interventions, data from NorPD and FD-Trygd will be obtained from inclusion in the trial until one year follow-up. The NorPD contains data about dispensed drugs in Norway, while FD-Trygd contains social security micro data for research. These data will be obtained retrospectively. The post-operative booklet that the patients receive as part of the iACT will also be collected at 6 months follow-up to assess if the patients used it as intended.

----- INSERT FIGURE 1-----

Survey data will be collected electronically by the use of laptops/smartphones. We will also utilize data from patients' medical records regarding surgical procedures and medical variables, as well as registry data, which will be linked to the survey data. Data from medical records as well as test results from blood samples will be entered directly into Viedoc by our study nurse. All data will be stored on a secure server at the hospital. The hospital already have a system in place for secure collection and storing of sensitive data which will be used.

A detailed plan for data management and sharing will be developed in collaboration with both Oslo University and the University of Oslo that shares the responsibility for data management in this study.

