### ***Inclusion criteria***

Patients must fulfill the following criteria to be eligible for inclusion in the study:

- Women diagnosed with breast cancer and scheduled for surgery
- Be able to provide informed consent
- Over the age of 18

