### ***Exclusion Criteria***

- Insufficient Norwegian speaking or writing skills to participate in the interventions and fill out questionnaires
- Over the age of 80
- cognitive and psychiatric impairment or
- other serious malignancies

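### Hypothesis 4 sick-leave days are counted without regard to work status and pooled with undefined benefits, which dilutes the comparison and costs power

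*Protocol*

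**What the plan says.** Under Aims and objectives, Hypothesis 4 predicts that hypnosis plus iACT "will result in fewer days of sick leave at 1 year follow-up compared to one-session mindfulness + TAU". Under Outcome Measures the quantity is wider: "we will use registry data to estimate the number of days participants in each group have been on sick leave (or other welfare benefits", over the year following surgery. The added benefits are not listed.

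Eligibility sets no work condition. The inclusion criteria are "Women diagnosed with breast cancer and scheduled for surgery", ability to consent, and "Over the age of 18". The exclusion criteria remove only those "Over the age of 80" at the upper end of the age range. Randomization is stratified by "type of surgery (mastectomy vs breast-conserving surgery) and whether the newly diagnosed breast cancer is a relapse or not", so neither age nor work status is balanced by design.

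Statistical analyses calls for intention-to-treat and per-protocol analyses and names no work-eligible subset. The data needed to define one are already planned: "Registry data on employment and benefit take-up and medical prescriptions will be obtained from FD-Trygd", covering inclusion to one year (Data collection and management).

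**The concern.** A woman who is retired or otherwise outside work cannot take sick leave. If only sick leave counts, she scores 0 days in either group. If a long-running benefit counts under the undefined addition, she may score close to 365 days in either group. Neither value can respond to hypnosis or iACT.

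Including such women does two things. It shrinks the difference in mean days, because part of each group has no effect to show. It also adds spread, because their fixed values lie away from the workers' mean. A real effect on sick leave could be missed, and the estimate would be hard to read as an effect on work. The outcome definition also goes beyond the hypothesis it is meant to test.

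**Working it through.** **The plan's own figures.** The protocol gives no sample size or power for sick leave. Its one fully specified calculation is for pain (1 point on NRS, SD 2.4, power 0.80, two-sided 0.05, 92 per group). It reproduces: 91 by the normal approximation, and 91.4 by the t-based one, rounded up to 92. It says nothing about sick-leave days.

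**Model.** Let q be the share not in work at inclusion, each scoring a constant c. Let workers have mean μ, SD σ and a true difference δ. There are n women per group, and the variance is taken as equal in the two groups.

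- All participants: difference (1-q)δ; variance (1-q)σ² + q(1-q)(μ-c)².
- Workers only: difference δ; variance σ²; group size n(1-q).
- Ratio of test statistics, workers to all: √(1 + q((μ-c)/σ)²).

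The ratio exceeds 1 whenever q > 0 and c differs from μ, even though the workers-only comparison uses fewer women. Its square is the equivalent ratio of sample sizes.

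**Numbers.** The values of q, μ, σ and c are assumptions; none is in the protocol.

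| Assumed μ, σ (days) | c | ((μ-c)/σ)² | q=0.2 | q=0.3 | q=0.4 |
|---|---|---|---|---|---|
| 100, 150 | 0 | 0.444 | 1.04 | 1.06 | 1.09 |
| 150, 110 | 0 | 1.860 | 1.17 | 1.25 | 1.32 |
| 100, 150 | 365 | 3.121 | 1.27 | 1.39 | 1.50 |
| 150, 110 | 365 | 3.820 | 1.33 | 1.46 | 1.59 |

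At c = 0 the squared ratios correspond to 9%, 13% and 18% more patients in the first row, and 37%, 56% and 74% more in the second. By this formula the 365-day case is the worse one whenever μ is below 182.5 days, the midpoint of 0 and 365.

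**Power under one further assumed set** (μ = 180, σ = 120, δ = 50 days, 100 per group, the two groups' variances averaged). If every woman could take sick leave, power would be 84%.

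| Share in work | Difference, all (days) | Power, all, c=0 | Power, all, c=365 | Power, workers only |
|---|---|---|---|---|
| 0.8 | 40 | 62% | 54% | 75% |
| 0.7 | 35 | 52% | 43% | 69% |
| 0.6 | 30 | 42% | 33% | 63% |
| 0.5 | 25 | 33% | 26% | 55% |

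Hypothesis 4 contrasts two of the four sequences created by the double randomisation. If 200 women split equally, that is about 50 per sequence. With 50 per group and the same assumptions, power is 15-36% counting everyone and 31-46% among workers.

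**Chance imbalance.** At q = 0.3 and 50 per group, the standard error of the difference in the share not in work is √(2 × 0.3 × 0.7 / 50) = 0.092. With workers at 150 days, an imbalance of that size moves the difference in means by about 14 days if c = 0 (0.092 × 150) or 20 days if c = 365 (0.092 × 215). This noise is already in the variance above.

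**The case against.** The strongest reply is that this is detail for a statistical analysis plan. The Outcome Measures sentence names a data source and a measure. It does not say that every participant must enter the comparison, and a subset fixed before randomisation is compatible with intention to treat. That stands in part: the protocol does not forbid the restriction. But it does fix the quantity as sick leave or other benefits, which is not what the hypothesis names. With no subset mentioned, the default is the whole sample.

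Second, mean days per randomised woman is a legitimate quantity, and the natural one for indirect costs. This stands, and is why all participants should stay in the economic analysis. It does not make it the best measure of an effect on sick leave.

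Third, the size is assumed throughout. This stands too: at q = 0.3 and c = 0 the factor is anywhere from 1.06 to 1.25 on the two sets of values tried, and q itself may be small.

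A reader might go further and infer that benefit status would swamp any work effect. The text does not support that. It does not say that old-age pension or benefits already in payment count, and the phrase can equally mean benefits that replace or follow sick leave. A reader might also infer that the trial could report a spurious work effect. Randomisation makes imbalance in work status a chance event that the standard error already reflects, so the false-positive rate is not raised.

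**Conclusion.** The point holds as one of efficiency and interpretation. With a share q of women not in work, the difference in days is diluted to (1-q) times the effect among workers, and precision is lost. The direction follows from the algebra, provided some women are not in work and their fixed count differs from the workers' mean. The size cannot be established from the protocol. For q between 0.2 and 0.4 and non-workers at 0 days, the workers-only test statistic is larger by about 4-9% (mean 100, SD 150) to 17-32% (mean 150, SD 110). It is larger still under both sets if full-year benefits count. There is no systematic bias. The primary outcomes, pain and fatigue at 3 months, and their sample size are unaffected. The matter is therefore minor to moderate, but worth correcting because the remedy is cheap.

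**What to change.** Amend the Hypothesis 4 paragraph under Outcome Measures as follows.

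- Make the main sick-leave comparison in participants who were in work at inclusion according to the FD-Trygd employment data. This status precedes both randomisations, so the comparison stays randomised. State that a woman with a job who is already on sick leave at inclusion counts as in work.
- Count sick-leave days, as the hypothesis states.
- Report other benefits separately, from a stated list that excludes benefits already in payment at inclusion.
- Report the all-participant day count as supportive, preferably adjusted for work status at inclusion. In the model above, adjustment removes the q(1-q)(μ-c)² term and so recovers the lost precision, but the difference stays diluted.
- Keep all randomised participants in the cost-utility analysis.

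The cost is a few sentences and no new data source. The extract starts at inclusion, so status on that date should fall within it; this should be confirmed when the data are ordered. The downside is that the sick-leave result then applies only to women in work and rests on fewer patients: 60 to 80 of every 100 if q is 0.2 to 0.4.
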